## **Procedures**

In brief, the Principal Investigator (PI) and or study staff will be provided with the contact information and or medical record numbers of interested participants from referring clinicians or health care professionals at the University of Ottawa Heart Institute, The Ottawa Hospital, along with family health teams, general practices and cardiology clinics in the Champlain region of Ontario. Each participant will be asked to complete the following: 1) screening, 2) baseline, and 3) 12 week exercise training program with pre and post measures. The anticipated duration of participation will be 16 weeks. It is possible that the duration of participation may be greater or less than 16 weeks based on participants’ schedule availability. Each component of the study is described in more detail below.

## **Recruitment and Screening**

We will contact clinicians or health care professionals from the University of Ottawa Heart Institute, The Ottawa Hospital, along with family health teams, general practices and cardiology clinics in the Champlain region of Ontario to inform them of this study. These clinicians or health care professionals will identify and refer potentially eligible patients with persistent or permanent atrial fibrillation interested in participating in an exercise training study to [name] and or a Research Coordinator (RC). Specifically, prospective research participants will be identified from clinicians or health care professionals at the University of Ottawa Heart Institute, The Ottawa Hospital, as well as partnering family health teams, general practices or cardiology clinics in the Champlain region of Ontario. If a patient expresses interest in participating in research to a health care professional within their circle of care, this will be acknowledged as permission to contact the prospective participant, in order to provide them with study information and determine interest and eligibility. The PI and or RC may also screen for eligible patients using vOACIS, OIBEE or other relevant UOHI databases. The PI and or RC may also screen patients coming to Heart Institute clinics for eligibility. The PI and or RC will only contact patients who have given permission to be contacted by research to provide them with information about the study and determine if they are interested in participating. Interested individuals will be contacted by the PI and or RC who will prescreen patients for eligibility and arrange a visit to confirm eligibility and obtain written, informed consent. Other methods of advertising that may be used include newsletters directed at hospital staff and advertisements run in local newspapers and on local radio stations. Approved posters and or flyers may also be distributed to pharmacies, seniors’ centers, community centers, recreation centers, cultural centers, churches, malls and libraries within the Champlain region. Secondary school students may volunteer to help with flyering in their community as part of the recruitment process. Additionally, the PI may have the opportunity to speak about her research surrounding exercise training in patients with atrial fibrillation on local TV and or radio stations. In this case, she may mention that recruitment is taking place for this study (OPPORTUNITY) and provide the email and or phone number of the RC. Furthermore, advertisements will be placed on the University of Ottawa Heart Institute’s public website, social media and the University of Ottawa Heart Institute’s Patient Alumni website and distribution list.

During the screening visit, the study staff will obtain participants' medical history, medication regime, age, sex, resting blood pressure and resting heart rate. Participants will also complete a cardiopulmonary exercise test on an electronically braked cycle ergometer (COSMED, USA) at the University of Ottawa Heart Institute Cardiac Diagnostic Centre or in the Track area of the Division of Prevention and Rehabilitation using a Carefusion Oxycon Mobile portable metabolic measurement system (p/n J143250). They will also undergo a medical assessment with a UOHI physician. Gender-related data will be collected retrospectively during one of the 1- to 10-year follow-up visits. Participants who have completed or have declined to participate in the 1- to 10-year follow-up visits will be contacted by phone and asked whether they would be willing to answer a set of questions related to their gender identity, relations and roles. Participants will be given a paper copy (in person during their follow-up visit or paper copy will be sent with a pre-paid envelope to their home address).

The study staff will record the participants' OHIP number to link their study information with the provincial health care database named Institute for Clinical Evaluative Sciences (IC/ES), to allow the study staff to track the use of health care services. Staff will use the IC/ES database to obtain data about emergency department visits, hospitalizations, day procedures and general/specialist visits. All linked data will be anonymized before being provided to us by IC/ES and all data will be analyzed and reported as group data, with no identifying information for any individual person reported or published. The OHIP number will be collected from the participants' medical chart using the University of Ottawa Heart Institute medical system. This information will be recorded in a password protected master list, located in the UOHI servers.

### **Baseline**

During the baseline phase, participants will perform a 6-minute walk test. Study staff will extract demographic and clinical information from the patient chart regarding medications, cardiovascular health, co-morbidities (e.g. diabetes, arthritis, peripheral vascular disease, cerebrovascular disease, chronic obstructive pulmonary disease), and exercise training status. It will not be possible to extract this information for patients that do not come from UOHI or TOH, so they will be asked to provide these details or the referring clinician/clinic may provide this information providing the participant has given their consent to do so. Height, body weight, waist circumference, fat mass, heart rate and blood pressure will be measured using standardized procedures and information regarding participant demographics and menopausal status (of female participants only) will be collected. Participants will perform standard load tests to assess lower body muscular fitness. They will be fitted with a Holter monitor and given a wear-time journal for completion over a 24-hour period. Participants will complete questionnaires assessing quality of life, symptom burden, activity status, depression and anxiety, sleep apnea, and insomnia. Participants will then be provided with an Actigraph motion sensor, to be worn for 7 days. They will complete a FITT log over this period of time to assist with the verification of the data collected while the monitor was worn. They will also complete a 7-day symptom diary to record any symptoms related to atrial fibrillation and a 7 day sleep diary to record sleep patterns. All participants will be asked if they are willing to complete an additional cardiopulmonary exercise test at baseline on a cycle ergometer using a Carefusion Oxycon Mobile portable metabolic measurement system. Only the subset of participants who are willing to do this measure will complete it.

### **Intervention**

Following the baseline phase, participants will be randomized in a 1:1 ratio to: 1) standard care + moderate-intensity continuous exercise training (to be completed in the University of Ottawa Heart Institute cardiovascular rehabilitation setting), or 2) standard care + high-intensity interval training using a blocked, stratified, random sequence that is computer-generated. Treatment assignments will be generated and placed in sealed, numbered envelopes to ensure concealment until baseline data are collected.

Participants will complete supervised exercise sessions that will take place in the Prevention and Rehabilitation Centre at University of Ottawa Heart Institute or in the *Goodlife* exercise facilities at The Ottawa Hospital – Civic Campus. Moderate-intensity continuous exercise training will follow cardiovascular rehabilitations guidelines: (1) warm-up for 5-10 minutes consisting of cardiovascular and or muscular endurance type activities at 20-35% of heart rate reserve for, rating of perceived exertion (RPE) of 6 to 11); (2) conditioning for 20-40 minutes at 40-85% heart rate reserve (or, RPE of 12 to 16); and, (3) cool down for 5-10 minutes at <60% heart rate reserve (or, RPE <12). Participants will attend on-site moderate-intensity continuous exercise training two times weekly for 12 weeks; they **will not attend educational workshops**. High-intensity interval training will include: (1) warm-up for 2 minutes at 50% of peak power output; (2) 2 x 8-minute interval training blocks (total: 16 minutes) of 30-seconds at 80-150% of peak power output interspersed with 30-seconds active recovery, four minutes of passive recovery will be permitted between the blocks; and (3) 1 minute cool down at 25% of peak power output after the last 30-second exercise bout. Participants will attend on-site high-intensity interval training two times weekly for 12 weeks. Blood pressure, heart rate and ratings of perceived exertion will be measured during the exercise sessions. Participants in the moderate-intensity continuous arm may undergo telemetry as is standard of care for cardiovascular rehabilitation. Pending the findings of telemetry, they may be asked to attend an additional medical appointment with a UOHI physician. Both the moderate-intensity continuous exercise and high intensity interval training arms will be encouraged to partake in moderate intensity aerobic exercise (RPE: 12-15) three to five additional times per week (aside from their two exercise sessions done at UOHI) for 30-60 minutes per session to accumulate approximately 200-400 total minutes of moderate intensity aerobic exercise per week. They will also be encouraged to do 2-3 strength training sessions throughout the week.

### **Follow Up Week 12**

During or following week 12 of the intervention (post), body weight, waist circumference, fat mass, heart rate and blood pressure will be measured using standardized procedures and information regarding participant demographics and menopausal status (of female participants only) will be collected. Participants perform standard load tests to assess lower body muscular fitness. They will be fitted with a Holter monitor and given a wear-time journal for completion over a 24-hour period. Participants will complete questionnaires assessing quality of life (Short Form 36; University of Toronto Atrial Fibrillation Severity Scale), symptom burden (Canadian Cardiovascular Society Severity of Atrial Fibrillation Scale), functional capacity (Duke Activity Status Index), anxiety and depression (Hospital Anxiety and Depression Scale, insomnia (Insomnia Severity Index) and sleep apnea (STOP-BANG Sleep Apnea Questionnaire). Participants will also complete a 6-minute walk test.

Participants will again be provided with an Actigraph motion sensor, to be worn for 7 days, and complete a daily FITT log over the 7-day period. They will also complete the 7-day symptom diary to

record atrial fibrillation symptoms and a 7 day sleep diary to record sleep patterns at the conclusion of the study.

All participants will be asked if they are willing to complete an additional cardiopulmonary exercise test at follow up on a cycle ergometer using a Carefusion Oxycon Mobile portable metabolic measurement system. Only the subset of participants who are willing to do this measure will complete it.

Boxes marked with an ‘x’ show which procedures will occur at each study visit or during each study week.

|                                                |           |                | Exercise Training |         |         |         |         |         |         |         |         |         |         |                | Follow Up                |
|------------------------------------------------|-----------|----------------|-------------------|---------|---------|---------|---------|---------|---------|---------|---------|---------|---------|----------------|--------------------------|
| Visit                                          | Screening | Baseline       | 1                 | 2       | 3       | 4       | 5       | 6       | 7       | 8       | 9       | 10      | 11      | 12             | Wk 26; Year 1 to year 10 |
| Length of time needed                          | 60 mins   | 3-3.5 hrs      | 1-2 hrs           | 1-2 hrs | 1-2 hrs | 1-2 hrs | 1-2 hrs | 1-2 hrs | 1-2 hrs | 1-2 hrs | 1-2 hrs | 1-2 hrs | 1-2 hrs | 3-3.5 hrs      | 35 mins                  |
| Informed consent                               | x         |                |                   |         |         |         |         |         |         |         |         |         |         |                |                          |
| Medical history                                | x         |                |                   |         |         |         |         |         |         |         |         |         |         |                |                          |
| Age                                            | x         |                |                   |         |         |         |         |         |         |         |         |         |         |                |                          |
| Sex (male/female)                              | x         |                |                   |         |         |         |         |         |         |         |         |         |         |                |                          |
| Height                                         |           | x              |                   |         |         |         |         |         |         |         |         |         |         |                |                          |
| Weight                                         |           | x              |                   |         |         |         |         |         |         |         |         |         |         | x              |                          |
| Waist circumference                            |           | x              |                   |         |         |         |         |         |         |         |         |         |         | x              | x                        |
| Fat mass                                       |           | x              |                   |         |         |         |         |         |         |         |         |         |         | x              | x                        |
| Resting blood pressure and heart rate          | x         | x              | x                 | x       | x       | x       | x       | x       | x       | x       | x       | x       | X       | x              | x                        |
| Exercise blood pressure and heart rate         |           |                | x                 | x       | x       | x       | x       | x       | x       | x       | x       | x       | x       | x              | x                        |
| Cardiopulmonary exercise test                  | x         | x (if willing) |                   |         |         |         |         |         |         |         |         |         |         | x (if willing) |                          |
| 24- hour Holter monitor                        |           | x              |                   |         |         |         |         |         |         |         |         |         |         | x              |                          |
| Muscular fitness (standard load tests)         |           | x              |                   |         |         |         |         |         |         |         |         |         |         | x              |                          |
| Physical activity levels (motion sensor)       |           | x              |                   |         |         |         |         |         |         |         |         |         |         | x              | x                        |
| 7-day FITT log                                 |           | x              |                   |         |         |         |         |         |         |         |         |         |         | x              | x                        |
| 7-day symptom diary                            |           | x              |                   |         |         |         |         |         |         |         |         |         |         | x              | x                        |
| 7-day sleep diary                              |           | x              |                   |         |         |         |         |         |         |         |         |         |         | x              | x                        |
| 6-minute walk test                             |           | x              |                   |         |         |         |         |         |         |         |         |         |         | x              | x                        |
| Questionnaires                                 |           | x              |                   |         |         |         |         |         |         |         |         |         |         | x              | x                        |
| Exercise training sessions done onsite at UOHI |           |                | x                 | x       | x       | x       | x       | x       | x       | x       | x       | x       | x       | x              |                          |

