### **Hypotheses**

In adults with persistent or permanent atrial fibrillation, a 12-week program of high-intensity interval training will be superior to moderate-intensity continuous exercise training in improving: 1) exercise capacity measured by 6-minute walk test distance; and, 2) quality of life measured by the physical component summary (PCS) measure of the Short Form 36 Health Survey Questionnaire (SF-36). Further, a 12 week program of high-intensity interval training will be superior to moderate-intensity continuous exercise training in improving: 1) exercise adherence measured by accelerometer (and verified by the 7-day FITT log; 2) activity status measured by the Duke Activity Status Index (DASI); 3 ) atrial fibrillation specific quality of life measured by the University of Toronto Atrial Fibrillation Severity Scale (AFSS); 4) symptom burden measured by the Canadian Cardiovascular Society Severity of Atrial Fibrillation (CCS-SAF) scale; 5) self-reported symptom frequency and severity measured by the 7-day symptom diary; 6) anxiety and depressive symptoms measured by the Hospital Anxiety and Depression Scale (HADS); 7) insomnia severity measured by the Insomnia Severity Index; 8) sleep apnea risk measured by the STOP-BANG Sleep Apnea Questionnaire; 9) self reported sleep patterns measured by the 7-day sleep diary; and, 10) HR control measured by 24-hour Holter ECG recordings and ECG recordings at each CPET; 11) lower body muscular fitness measured by standard load tests; and 12) exercise capacity measured by cardiopulmonary exercise test (CPET) [in a subset of willing participants].

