9. Self reported sleep patterns: will be measured using a 7-day sleep diary. This will be used to capture any sleep problems and measure any progress in improving sleep. Details regarding sleep timing, quality, naps, alcohol consumption and sleep medication will be collected over a 7-day period.

10. Heart rate control: measured using 24-hour Holter ECG recordings and ECG recordings at each CPET.

11. Muscular fitness: measured using standard load tests. This test involves the completion of repetitions of leg press exercises, at a defined resistance of 40 kg at a cadence of 22 repetitions per minute (set by a metronome). The maximum number of repetitions done before falling behind the required cadence will be recorded.

12. Exercise capacity: measured using a gold standard symptom-limited, cardiopulmonary exercise test (CPET) on an electronically braked cycle ergometer using a ramp protocol. Gas exchange will be monitored continuously; the highest rate of oxygen uptake achieved (i.e. peak  $\text{VO}_2$  in mL/kg/min) during the last minute of the CPET will represent exercise capacity. All participants will be asked if they are willing to complete this measure at baseline and follow up and only those who are willing will complete it.

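### Peak VO2 (secondary outcome 12) is compared in volunteers whose week-12 willingness is given after randomisation, and the screening CPET that every participant has is not made its baseline

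*Protocol*

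**What the plan says.** The Hypotheses section lists, as its twelfth secondary comparison, superiority of interval training on "exercise capacity measured by cardiopulmonary exercise test (CPET) [in a subset of willing participants". Secondary Measures, item 12, makes the outcome the highest oxygen uptake "during the last minute of the CPET will represent exercise capacity" and has the test done "at baseline and follow up and only those who are willing will complete it".

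Willingness is asked twice. The Baseline section says: "All participants will be asked if they are willing to complete an additional cardiopulmonary exercise test at baseline on a cycle ergometer", and adds: "Only the subset of participants who are willing to do this measure will complete it". Follow Up Week 12 asks again: "All participants will be asked if they are willing to complete an additional cardiopulmonary exercise test at follow up on a cycle ergometer". The procedures table in that section marks both tests as conditional on willingness. The Intervention section places randomisation after the baseline phase, so between the two requests.

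Screening is different. Recruitment and Screening says: "Participants will also complete a cardiopulmonary exercise test on an electronically braked cycle ergometer (COSMED, USA"; it names the same portable metabolic system as the optional tests, and the table marks this test without condition. Additional Measures describes the CPET used for exercise prescription in both arms as a symptom-limited ramp test on an electronically braked cycle, with VO2 from expired gas, and labels it as measured only at baseline.

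Analyses of Results plans repeated measures mixed models for primary and secondary outcomes and does not say which CPET value serves as baseline.

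**The concern.** Willingness to repeat a maximal test at week 12 is a choice made after allocation, by someone who knows which training they received. It can depend on arm, on how the training was tolerated and on whether the participant feels fitter. If it does, the two groups of volunteers differ for reasons other than the training, and comparing them is no longer a comparison of randomised groups.

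Item 12 also takes its baseline reading from an optional test, although a pre-randomisation reading on the same metabolic system exists for everyone. A participant who declines the optional baseline test but does the week-12 test has no pre-training value from the tests that define the outcome, yet does have one from screening. What is at stake is precision, and the ability to describe and partly adjust for who is missing at week 12, in a secondary comparison that carries a superiority hypothesis.

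**Working it through.** The Protocol gives no sample size, power, SD or willing share for the CPET subset, so there is no figure of its own to reproduce. The check is a comparison of sections, followed by illustrations on assumed inputs.

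**1. Order of events.** Screening CPET (all participants), optional baseline CPET, randomisation, 12 weeks of training, optional week-12 CPET. No section limits the week-12 test to those who agreed before randomisation.

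**2. Is the screening test usable as baseline?** The prescription needs a CPET in every participant, and the baseline-phase test is optional. The universal test in Additional Measures can therefore only be the screening one, despite its label. On that reading it matches item 12 in type of ergometer, ramp protocol, symptom limit and gas exchange. The Recruitment and Screening section does not itself mention the ramp or the symptom limit, so the match rests on reading the two sections together.

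**3. Number of pairs.** Inputs: N = 108 (Sample Size); willing share w_B at baseline and w_F at week 12 (assumed).

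- Optional baseline, independent choices: pairs = N × w_B × w_F.
- Screening as baseline: pairs = N × w_F.
- Added pairs, independent choices: N × w_F × (1 − w_B).
- Added pairs if everyone willing at week 12 was also willing at baseline (nested): 0.

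At 60% per visit, independent: 108 × 0.6 × 0.6 = 38.9, about 39; 108 × 0.6 = 64.8, about 65; added 25.9, about 26. At 60% nested: 65 either way.

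Other assumed shares, independent choices:

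| w_B | w_F | Pairs, optional baseline | Pairs, screening baseline | Added |
|---|---|---|---|---|
| 50% | 50% | 27.0 | 54.0 | 27.0 |
| 50% | 70% | 37.8 | 75.6 | 37.8 |
| 50% | 90% | 48.6 | 97.2 | 48.6 |
| 70% | 50% | 37.8 | 54.0 | 16.2 |
| 70% | 70% | 52.9 | 75.6 | 22.7 |
| 70% | 90% | 68.0 | 97.2 | 29.2 |

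**4. What the mixed model already keeps.** At 60% independent, about 39 have both optional tests, 108 × 0.6 × 0.4 = 25.9 have baseline only, another 25.9 have week 12 only, and 108 × 0.4 × 0.4 = 17.3 have neither. So 108 − 17.3, about 91, have at least one reading that a mixed model can use. The screening value adds a baseline for the 26 with week 12 only; it does not add 26 people to the analysis.

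**5. Selection at week 12.** Assume no true effect, and a normally distributed willingness score with correlation ρ to the change in peak VO2, the same in both arms. The spurious difference, in SDs of the change, is ρ × (m(b) − m(a)), where a and b are the willing shares in the two arms and m(s) is the mean of the top share s of a standard normal variable. By simulation:

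- 80% v 60% willing: 0.059 at ρ = 0.2, 0.147 at ρ = 0.5.
- 70% v 50% willing: 0.060 at ρ = 0.2, 0.150 at ρ = 0.5.
- 70% v 70% willing: 0 at either ρ.

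For scale, the difference detectable with 80% power at two-sided 5%, before any baseline adjustment, is (1.96 + 0.84) × √(2/n per arm). That is 0.64 SD at 70% willing at week 12 (n = 37.8 per arm) and 0.76 SD at 50% (n = 27).

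**The case against.** The restriction to volunteers is declared openly and repeatedly, and the measure is the last of twelve secondary ones. Keeping an extra maximal test optional limits burden. A second baseline test after a first exposure is defensible, because it may carry less learning effect. All of this stands, and it is why the point is minor.

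A reader might infer that participants without an optional baseline test drop out of the analysis, so that 39 would be analysed instead of 65. The Protocol does not say so. No section requires complete pairs or rules out the screening value, and a mixed model can use a single visit. The 60% and the independence are assumptions; people willing once are probably more likely to be willing again, which moves the gain towards zero.

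It can also be said that the choice of baseline reading belongs to a statistical analysis plan that is not shown. That would hold if the Protocol were silent. But item 12 itself names the optional tests at baseline and follow-up as the measure, and the universal CPET appears only among the additional measures, for prescription.

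Finally, a new baseline does not cure selection at week 12. That is correct and limits what the fix can claim.

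**Conclusion.** The point holds as a minor one. The peak VO2 comparison rests on volunteers who decide at week 12, after randomisation, and the Protocol leaves a universal pre-randomisation reading unused as the baseline for this outcome.

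The benefit of using it is some precision and some reduction of bias, of unknown size. Added pairs run from none (nested choices) to about 26 of 108 (60%, independent), and from about 16 to 49 over the other independent combinations tried. The gain in information is smaller than these counts suggest under the planned mixed model. Conditioning on screening VO2 deals with missingness that depends on baseline fitness, but not with selection on tolerance or perceived improvement.

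Two stronger readings are not supported. One is that the comparison is shown to be biased: the illustrated 0.06 to 0.15 SD needs a 20-point gap in willingness between arms and an assumed correlation, and it vanishes with equal shares and equal selection. The other is that the trial's conclusion on exercise capacity is at risk: the primary measure is the 6-minute walk test, which carries no willingness condition, and no section says that the CPET result will be read alongside it.

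**What to change.** In Secondary Measures, item 12, and in Analyses of Results:

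- Name screening peak VO2 as the baseline value or covariate for all randomised participants.
- Analyse week-12 peak VO2 by assigned arm in everyone with a week-12 test, whether or not they did the optional baseline test. That test can be kept as a second baseline reading.
- Report, by arm, week-12 CPET completion and the screening peak VO2 of completers and non-completers.
- Label the result exploratory and say that selection after randomisation remains possible. The ECG recordings taken at each CPET for heart rate control need the same caution.
- Reconcile the baseline-only label in Additional Measures with the placing of the universal CPET at screening.

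The cost is wording: no new visit and no new test. The downside is that the screening value may carry more learning effect; as it precedes randomisation, this should affect both arms equally. Removing the remaining selection would need more than this, such as a week-12 test planned for everyone, or agreement recorded before randomisation with non-completers treated as missing data. The first of these adds burden.
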